## Abstract

**Introduction:**

National guidance for chronic obstructive pulmonary disease (COPD) suggests that self-management support be provided for patients. Our institution has developed a standardised, manual-based, supported self-management programme: Self-Management Programme of Activity Coping and Education (SPACE for COPD(C)). SPACE was previously piloted on a 1-2-1 basis, delivered by researchers, to individuals with COPD. Discussions with stakeholders highlighted considerable interest in delivering the SPACE for COPD(C) intervention as a group-based self-management programme facilitated by healthcare professionals (HCPs) in primary care settings. The study aims are to explore the feasibility, acceptability and efficacy for the intervention to be delivered and supported by HCPs and to examine whether group-based delivery of SPACE for COPD(C), with sustained support, improves patient outcomes following the SPACE for COPD(C) intervention.

**Methods and analysis:**

A prospective, multi-site, single-blinded randomised controlled trial (RCT) will be conducted, with follow-up at 6 and 9 months. Participants will be randomly assigned to either the control group (usual care) or intervention group (a six-session, group-based SPACE for COPD(C)self-management programme delivered over 5 months). The primary outcome is change in COPD assessment test at 6 months.

A discussion session will be conducted with HCPs who deliver the intervention to discuss and gain insight into any potential facilitators/barriers to implementing the intervention in practice. Furthermore, we will conduct semi-structured focus groups with intervention participants to understand feasibility and acceptability. All qualitative data will be analysed thematically.

**Ethics and dissemination:**

The project has received a favourable opinion from South Hampshire B Research Ethics Committee, REC reference: 14/SC/1169 and full R&D approval from the University Hospitals of Leicester NHS Trust: 152408.

Study results will be disseminated through appropriate peer-reviewed journals, national and international respiratory/physiotherapy conferences, via the Collaboration and Leadership in Applied Health Research and Care and through social media.

**Trial registration:**

ISRCTN17942821; pre-results.

Strengths and limitations of this studyThe burden of chronic obstructive pulmonary disease (COPD) is significant to both the health service and the individual. Supported self-management is important, but options are limited for those with COPD. This study explores a group-based supported self-management programme for individuals with COPD.This is a pragmatic trial where the study intervention (a group-based self-management support intervention for people with COPD) will be delivered and supported by healthcare professionals in community settings. The study has been designed to align with how the intervention might be delivered in routine clinical practice.Our follow-up period is 3 months post-intervention. Unfortunately, due to funding constraints, we are unable to carry out a longer term follow-up.

## Introduction

Chronic obstructive pulmonary disease (COPD) is the third leading cause of death worldwide and is associated with considerable disability, impaired quality of life and high utilisation of healthcare resources.^1^ Symptoms and manifestations of the disease can be modified by adopting appropriate health behaviours including, but not limited to, exercise, physical activity, smoking cessation, anxiety management, breathing control, medication adherence and exacerbation management.^2^ Acknowledging the importance of the role of the patient in adopting these behaviours, there has been a shift in attitude from a traditional paternalistic model of care towards a more collaborative approach for chronic disease management. The National Health Service (NHS) Five Year Forward View’s aim is for the NHS to become better at helping people to manage their own health by staying healthy, making informed choices of treatment, managing conditions and avoiding complications.^3^ Inevitably, the patient is predominantly responsible for administering their own care and making choices about health behaviours that will affect their outcomes. Self-management support aims to inform and support patients in making these choices. National and international guidelines for the management of COPD suggest that self-management support should be provided for people with COPD, though at present evidence for how and when that support should be delivered is less robust.^2^

Reports in the literature describe programmes that have targeted interventions for patients who have been hospitalised with a COPD-related admission, often with the primary ambition of reducing future admissions.^4^ These studies have had little impact on readmission. Arguably, the offer of supported self-management should be offered earlier in the disease trajectory. Other COPD self-management programmes beyond the UK have been described in a stable population. Although the models of care delivered are quite heterogeneous,^5^ with some programmes providing up to 2 years of weekly supervised exercise training and education.^3 6–8^ The infrastructure and resources required to provide such comprehensive support means they are unlikely to be deliverable to the breadth of the COPD population in the UK. In order to address this, we previously developed and tested a new self-management programme that offered a ‘light touch’ approach so that it could be provided on a larger scale.

A Self-Management Programme of Activity Coping and Education—SPACE for COPD(C)—aims to support people with COPD in managing day-to-day tasks, minimise symptom burden, provoke health enhancing behaviour change and enhance emotional well-being. The programme is structured around the SPACE for COPD(C) manual, which combines both generic self-management skills and disease-specific tasks. Pilot testing assessed the feasibility and acceptability of the intervention to patients,^9^ and a fully powered randomised controlled trial assessed the efficacy of the intervention in primary care,^10^ powered for change in symptom burden measured by the self-reported Chronic Respiratory Questionnaire (CRQ-SR) dyspnoea domain at 6 months. In these studies, the SPACE for COPD(C) manual was introduced to patients during an initial consultation with a healthcare professional (HCP) (using motivational interviewing techniques), followed by two telephone calls during the subsequent 6 weeks. Secondary outcomes included other domains of the CRQ-SR, shuttle walking tests, disease knowledge, anxiety, depression, self-efficacy, smoking status and healthcare utilisation measured at baseline, 6 weeks and 6 months follow-up. Results demonstrated significant short-term improvements in CRQ-SR dyspnoea, anxiety, fatigue and emotion scores, exercise performance and disease knowledge. At 6 months, anxiety, exercise performance and smoking status outcomes remained significantly different between the intervention group and the usual care group, though there was no between-group difference in change in CRQ-SR dyspnoea.

Implementation focused work carried out following these studies with HCPs in primary care and local Clinical Commissioning Groups (CCGs), demonstrated considerable interest in delivering the SPACE for COPD(C) intervention as a group-based intervention rather than on a one-to-one basis. The most common theoretical rationale underpinning delivery of group-based self-management support interventions is Social Cognitive Theory/Social Learning Theory.^11 12^ Bandura’s (1977, 1997) social learning theory posits that behaviour is influenced by beliefs about one’s ability to perform a particular behaviour (self-efficacy expectations), beliefs about the effectiveness of the behaviour (eg, the advantages and disadvantages of performing this behaviour; outcome expectations) and learning through social observation (including social norms, social support or pressure and the behaviours of others). Peer support and use of other patients as role models are approaches grounded in this theory and directly applicable to group-based self-management support interventions.

Delivery of SPACE for COPD(C) as a group-based intervention allows for several face-to-face contacts between patients and HCPs over a number of sessions. These contacts could be spread out further across a longer period, which may be more successful in maintaining behaviour change. Furthermore, having earlier sessions closer together in time allows group cohesion to take place, an important factor in optimising group dynamics.^13^

The SPACE for COPD(C) intervention has also previously been delivered by a member of the research team rather than by existing clinical services. If the group-based intervention were to be implemented in primary care following the current study, importance would be placed on delivery by HCPs in a format that is feasible and acceptable to HCPs, health service providers and to patients. Understanding how this intervention can be delivered within existing health services and identifying key barriers and facilitators to its implementation is an important next step in the development of this complex intervention.

### Aims and objectives of the study

This study aims to:Examine whether group-based delivery of SPACE for COPD(C), with sustained support, improves patient outcomes following the intervention compared with a control group;Explore feasibility, acceptability and efficacy of the intervention to be delivered and supported by HCPs. This will be done by:Exploring HCP’s experiences of delivering the intervention and identify any barriers to delivery in practice;Understanding, from the patient perspective, the feasibility and acceptability of the SPACE for COPD(C) intervention delivered by HCPs in a group-based community setting.

## Methods/design

### Study design

The trial is a prospective, multi-site, single (assessor) blinded randomised controlled trial comparing a community-based, HCP-led, group-based self-management programme based on the SPACE for COPD(C) manual with usual care. The design of the study and flow of participants is described in figure 1. The study will be run across Leicestershire and Rutland, and a total of 150 participants will be recruited (75 in the intervention group and 75 in the control group).

**Figure 1 F1:**
[figure not shown]
Participant flow through the study.

### Recruitment of participants

We will recruit participants with COPD, who will be identified from primary care (General Practice; GP) COPD registers and from patients who respond to a poster advertisement that will be displayed at GP practices and hospitals. We will also recruit participants from the following areas within the Respiratory Biomedical Research Unit at University Hospitals of Leicester:Those who have been involved in previous research trials who have agreed to be contacted again; orThose who were unsuitable for previous research trials but who agreed to be contacted about future research trials for which they might be eligible.

### Participant invitation

Eligible individuals identified as having an established diagnosis of COPD are sent an invitation letter, a patient information sheet about the study and a reply slip. For those recruited directly from primary care, the invitation letters are sent by the primary care practice where the search was conducted. For those recruited from existing databases, the invitation is sent from the principal investigator of the study. Individuals who are interested in taking part are asked to return a reply slip directly to the SPACE for COPD(C) research team. Interested participants are then contacted via their preferred contact method, and an appointment is arranged for a baseline visit.

### Eligibility criteria

Participants are eligible for the trial if they have:An established diagnosis of COPD as defined by The Global Initiative for Chronic Obstructive Lung Disease (GOLD) criteria.

Patients are excluded from participating in the trial if they are:Unable to participate in the exercise component of the SPACE for COPD(C) programme due to neurological, locomotive or psychiatric disability;Unable to participate in the exercise component of the SPACE for COPD(C) programme due to other comorbidities where exercise would be a contraindication (e.g., unstable angina);Unable to read/write English to the level of an 8 year old;Unwilling to be randomised;Previous participants of pulmonary rehabilitation or have received the SPACE for COPD(C) manual in the previous 12 months.

### Randomisation

Once participants have consented to take part in the study and spirometry has confirmed a COPD diagnosis, participants are randomised by an unblinded member of the study team using an online randomisation tool (sealed envelope).^14^ Individuals are randomised (1:1) to the control group or the intervention (SPACE for COPD(C) group-based self-management programme) group. The system randomises patients in random permuted blocks. This allows for the 1:1 ratio, but due to the random permuted blocks of 2, 4 or 6 ensures full randomisation. Simple randomisation has been chosen as there has been no requirement to stratify by age, gender, location or other variables. Participants are immediately informed of their allocated treatment by an unblinded member of the study team. Unblinding is permissible in the case of medical emergencies (eg, cardiac arrest) or patients being admitted to hospital for an exacerbation.

### Study interventions

#### Usual care (control group)

Participants in the control group will continue with any usual check-ups/reviews, and there will be no additional care provided or removed from their current access. If patients are referred to pulmonary rehabilitation in the duration of their time in the study, they will not be denied access to the programme; however, they will not be included in the final analysis due to the use of ‘intention-to-treat’ analysis. No additional advice, information or recommendations will be provided to participants in this group.

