### Study outcomes

Data will be collected during baseline, 6-month and 9-month appointments at the Leicester Respiratory Biomedical Research Unit by trained members of the study team. Data are collected following standardised operating procedures. Written informed consent is obtained from all participants prior to the commencement of data collection. Details of all clinical assessments and outcome measures are provided in table 3. General practitioners are informed of patients’ participation in the trial and any relevant results. Any serious adverse events will be reported to the sponsor and patients’ ability to exercise safely will be monitored.

**Table 3 T3:** Details of study clinical assessments and outcome measures at all appointments

Baseline appointment (blinded and unblinded study team members)	6-month appointment (blinded study team member)	9-month appointment (blinded or unblinded study team member)
Consent Collection of demographic details and medical history Blood pressure Spirometry Randomisation* Questionnaires (CAT, EQ-5D, CRQ-SR, BCKQ, PAM, HADS)* Shuttle walking tests* (intervention participants only): 2xISWT; 1xESWT Participants given Senswear activity monitor to wear for 7 days*	Check consent Questionnaires (CAT, EQ-5D, CRQ-SR, BCKQ, PAM, HADS) Shuttle walking tests† Participants given Senswear activity monitor to wear for 7 days	Check consent Questionnaires (CAT, EQ-5D, CRQ-SR, BCKQ, PAM, HADS) Shuttle walking tests Participants given Senswear activity monitor to wear for 7 days

*Carried out by an unblinded member of the study team.

†ESWT carried out by an unblinded member of the study team.

BCKQ, Bristol COPD Knowledge Questionnaire; CAT, COPD Assessment Test; CRQ-SR, Chronic Respiratory Questionnaire; EQ-5D, European Quality of Life-5 Dimensions; ESWT, endurance shuttle walking test; ISWT, incremental shuttle walking test; HADS, Hospital Anxiety and Depression Questionnaire.; PAM, Patient Activation Measure.

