### Primary outcome

The primary outcome is health status, as measured by the COPD Assessment Test (CAT)^16^ at 6 months post-baseline. This measure was chosen due to ease of use in clinical practice compared with the Chronic Respiratory Questionnaire (as used in the previous RCT). The CAT is a validated, short (eight items) and simple patient completed questionnaire and assesses globally the impact of COPD (cough, sputum, dyspnoea and chest tightness) on health status. The CAT is scored 0–5 with a range of 0–40; scores of 0–10, 11–20, 21–30, 31–40 represent mild, moderate, severe or very severe clinical impact, respectively.

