#### Quantitative analysis

This will primarily be completed on an intention-to-treat analysis. All quantitative data will be assessed for normality and analysed using appropriate parametric and non-parametric statistics (eg, within and between measures t-tests and analyses of variance); statistical significance will be set at p=0.05. Secondary per protocol analyses will be carried out.

A post hoc analysis will be carried out, which will exclude patients in either arm that received pulmonary rehabilitation as part of their usual care. We would anticipate that patients who participate within the study will not require pulmonary rehabilitation. However, due to pulmonary rehabilitation being a part of ‘best’ usual care, this will not be withheld from the patient.

Quantitative data for all outcomes will be transcribed from the case report form (CRF) onto an electronic database. A statistical software package will be used to carry out quantitative analyses. Predictive analytics software (SPSS; Statistical Package for the Social Sciences) will be used to analyse the data, the licence for which is provided by University Hospitals of Leicester NHS Trust. Continuous variables will be presented as mean and SD or median and IQR, and categorical data will be presented as frequencies and percentages. Data will be checked for normality and appropriate parametric and non-parametric tests will be used. Any baseline differences will be adjusted for. Any missing data will be imputed, and both intention-to-treat and per-protocol analyses will be conducted.

We have not secured funding for a healthcare utilisation analysis but would anticipate further CLAHRC (Collaboration and Leadership in Applied Health Research and Care) funding if the trial is clinically effective.

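### The rule excluding patients for pulmonary rehabilitation has no cut-off at the 6-month visit, so it discards primary outcomes that later rehabilitation could not have affected

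*Protocol article*

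**What the plan says.** The article deals with pulmonary rehabilitation in two places.

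- **Usual care (control group).** The trigger is a referral: "If patients are referred to pulmonary rehabilitation in the duration of their time in the study". The consequence is that "they will not be included in the final analysis due to the use of" intention-to-treat. The time window is the patient's whole time in the study.
- **Quantitative analysis.** The analysis is primarily by intention to treat. A separate post hoc analysis will "exclude patients in either arm that received pulmonary rehabilitation as part of their usual care". The trigger here is rehabilitation received, it applies to both arms, and no date is attached. The same paragraph says that the investigators do not expect participants to need rehabilitation.

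On timing, the abstract describes a trial "with follow-up at 6 and 9 months" and states: "The primary outcome is change in COPD assessment test at 6 months". The Primary outcome section also places the CAT at 6 months after baseline. The last visit therefore falls three months after the primary outcome is recorded.

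**The concern.** An exclusion for rehabilitation can serve a purpose only if the rehabilitation could have changed the outcome being compared. Rehabilitation that follows a referral made after the 6-month visit cannot change a CAT score already recorded at that visit. Removing that patient from the 6-month comparison takes away a valid primary outcome and isolates nothing.

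The loss may not be neutral. If patients with a heavier symptom burden around month 6 are more likely to be referred soon afterwards, those removed will tend to have poor 6-month CAT changes. If mainly controls are removed, the remaining control group looks better than the randomised one, and a true benefit of the programme is pulled towards zero.

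This differs from asking whether such an exclusion belongs in an intention-to-treat analysis at all. Moving the exclusion to a secondary analysis would still leave it undated for a 6-month outcome.

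**Working it through.** **1. Timing.** Take a control who attends the 6-month visit, completes the CAT, and is referred in month 7 or 8.

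| | Usual care section | Quantitative analysis section |
|---|---|---|
| Trigger | referred | received |
| Arms | text stands under the control group | either arm |
| Window | whole time in study (to month 9) | none stated |
| Referred in month 7, attends by month 9 | removed | removed from the post hoc analysis |
| Referred in month 7, never attends | removed | kept |
| Could it have affected the 6-month CAT? | no | no |

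**2. Baseline for the size.** Study power gives a difference of 2.5, SD 5.0, two-sided α 0.05 and 60 evaluable per group for 80% power. The standard error is 5 × √(2/60) = 0.91, so power is Φ(2.5/0.91 − 1.96) = 78.2%. This is close to the stated 80%, for which 63 per group would be needed. That small gap is a separate matter and does not affect this point.

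**3. Assumptions not in the documents.** A share q = 5-15% of controls (3 to 9 of 60) is referred after month 6. The correlation ρ between the tendency to be referred and a poor 6-month CAT change is 0 to 0.5.

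**4. Controls only removed (Usual care rule).** Removing the top share q on a normal referral score moves the control mean by ρ × SD × φ(z)/(1 − q), where z is the upper-q normal point. For q = 10% and ρ = 0.5: 0.5 × 5 × 0.1755/0.90 = 0.49, so a true 2.5 is estimated as 2.01. Power uses SE = 5 × √(1/(60(1 − q)) + 1/60).

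| q | ρ = 0: bias, power | ρ = 0.3: bias, power | ρ = 0.5: bias, power |
|---|---|---|---|
| 5% | 0, 77.1% | 0.16, 71.5% | 0.27, 67.4% |
| 10% | 0, 76.0% | 0.29, 65.3% | 0.49, 57.4% |
| 15% | 0, 74.7% | 0.41, 59.2% | 0.69, 47.8% |

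All biases run against the intervention. The largest is 0.69/2.5, about 27% of the target difference.

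**5. Same rule in both arms (post hoc analysis).** A true benefit of 2.5 is 0.5 SD, so the intervention arm's referral cut-off is z + 0.5ρ and fewer of its patients are removed. The bias is the difference between the two arms' shifts. For q = 15% and ρ = 0.5, 9.9% of the intervention arm is removed and the shifts are 0.69 and 0.48, leaving a bias of about 0.20 (estimate 2.30, power 65.3%). For q = 5% and ρ = 0.3 the bias is 0.04. At ρ = 0 it is zero, with power of 76.1% to 71.4%. This calculation removes everyone referred. The section's trigger is rehabilitation received, which fewer patients will meet, so these figures are probably on the high side.

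**The case against.** **The analysis section already keeps the primary analysis by intention to treat.** It confines the exclusion to a post hoc analysis in either arm. If that section governs, the bias is at most about 0.2 CAT points, roughly 0.2 of a standard error (0.20/0.91), in a non-primary analysis. This stands, and it limits the weight of the point. It does not dispose of it, because the Usual care section says something else and the post hoc rule is undated too.

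**An undated window is detail for an analysis plan.** For the post hoc analysis alone that would be a fair answer. The Usual care section, however, states a window, and that window does not suit a 6-month outcome.

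**Rehabilitation is expected to be rare.** The investigators anticipate no need for it. With no referrals after month 6 the effect is nil. The 5-15% range is an assumption, not a forecast.

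**The outcome itself may be read as causing the exclusion.** A reader might infer this because general practitioners are told of "participation in the trial and any relevant results". The documents do not support it: they do not say that the CAT is among those results, or that any trial result prompts a referral. A shared cause, current symptom burden, is plausible but is likewise not stated. At zero correlation the harm is lost precision only.

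**Rehabilitation may seem to go unrecorded, or to be noticed unevenly between arms.** A reader might infer this because Table 3 lists no such item, although "Details of all clinical assessments and outcome measures are provided in table 3". That does not follow. Rehabilitation received as usual care is neither a clinical assessment nor an outcome measure, and the article mentions a case report form that is not shown. No passage describes how rehabilitation is ascertained in either arm.

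**Conclusion.** The point holds as a badly set rule. Followed as written, the Usual care section removes recorded 6-month outcomes because of later events that could not have affected them. The two sections also disagree on the trigger and on the arms covered. Loss of valid data is certain for any patient caught this way. Bias is conditional on referral being related to symptom burden around month 6.

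With 5-15% of controls referred after month 6 and a correlation of 0-0.5, the bias is 0 to about 0.7 CAT points if the Usual care rule governs, and 0 to about 0.2 in a both-arm secondary analysis. Neither the rate nor the correlation comes from the documents. A fall in power from 78% to 57% should not be quoted as the expected consequence. It needs the Usual care rule to override intention to treat, 10% of controls referred, and the highest correlation assumed. The sponsor should correct the rule, but the documents do not show that the primary result will be materially distorted.

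**What to change.** 1. Reconcile the two sections. State that the primary intention-to-treat analysis keeps all randomised patients whatever their rehabilitation status, and delete the exclusion from the Usual care section. Rewording that exclusion from referral to attendance would not be enough.
2. Keep the rehabilitation-excluding analysis as secondary, in both arms, with one trigger: rehabilitation attended.
3. Tie it to the visit analysed. For the 6-month CAT, count only rehabilitation begun before the date of that CAT. Rehabilitation begun between the 6- and 9-month visits bears only on the 9-month analysis.

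The cost is a few sentences of analysis text, with no extra patients or visits and no change to access to rehabilitation. Start dates are needed in both arms; if the case report form does not already hold them, one identically worded line at 6 and 9 months would do, relying on patient recall. The secondary analysis still conditions on an event after randomisation, since rehabilitation before month 6 may also reflect worsening. It should be read as supportive only.

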### Data analysis

#### Study power

The power calculation was based on the primary outcome at 6 months.^30 31^ To detect a mean±SD between-group difference of 2.5±5.0 in the change in CAT with 80% power, 60 people per group are required (α=0.05, two tailed). In anticipation of a possible 25% attrition rate, the total sample size was increased to 75 per group (150 in total).

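### The usual-care section drops patients referred to pulmonary rehabilitation from the final analysis and cites intention-to-treat as the reason; this inverts the principle and contradicts the analysis section

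*Protocol article*

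**What the plan says.** Two sections of the protocol article deal with patients who go on to pulmonary rehabilitation.

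- **Usual care (control group).** Access is preserved: "If patients are referred to pulmonary rehabilitation in the duration of their time in the study, they will not be denied access to the programme". The same sentence then says of these patients that "they will not be included in the final analysis due to the use of ‘intention-to-treat’ analysis".
- **Quantitative analysis.** The general rule is "This will primarily be completed on an intention-to-treat analysis". A further analysis, labelled post hoc, is planned "which will exclude patients in either arm that received pulmonary rehabilitation as part of their usual care". The section expects few such cases ("We would anticipate that patients who participate within the study will not require pulmonary rehabilitation") but adds that "due to pulmonary rehabilitation being a part of ‘best’ usual care, this will not be withheld from the patient". It closes with "Any missing data will be imputed, and both intention-to-treat and per-protocol analyses will be conducted".

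**The concern.** ITT is a reason to keep patients in the analysis. It cannot be the reason for leaving them out because of something that happened after randomisation. The sentence in the usual-care section therefore states a rule and a justification that cancel each other, and the rule conflicts with the analysis section.

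The primary comparison is at stake. Referral happens after randomisation and plausibly depends on symptoms. It may also depend on allocation: the Randomisation section has participants told their arm at once, and the Study outcomes section has general practitioners told that their patient is in the trial. Removing referred patients is therefore a selection that randomisation does not protect.

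It also changes the question. The comparator is usual care with nothing taken away, and the protocol counts rehabilitation as part of the best version of that care. Without the referred controls, the comparator becomes usual care among those who did not appear to need rehabilitation.

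**Working it through.** **1. The two sections side by side**

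| Feature | Usual care (control group) | Quantitative analysis |
|---|---|---|
| Analysis that excludes | The final analysis | A separate analysis, called post hoc |
| Arm | Control, from the heading and surrounding sentences; the sentence itself says only patients | Either arm |
| Trigger | Referral | Receipt |
| Stated reason | ITT | None tied to ITT; ITT is the primary principle |

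They differ on analysis, arm and trigger. A separate analysis without rehabilitation patients has a purpose only if the primary analysis contains them, so both sections cannot be followed. The planned imputation does not settle it, because the usual-care text removes patients rather than leaving values missing.

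**2. Planning figures (Study power section)**

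The inputs are a difference of 2.5 and an SD of 5.0 in change in CAT, two-sided α = 0.05, 80% power, and 60 per group.

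- n per group = 2 × [5.0 × (1.960 + 0.842) / 2.5]² = 62.8, so 63. The stated 60 is not reproduced.
- At 60 per group, SE = 5 × √(1/60 + 1/60) = 0.913, and power = Φ(2.5/0.913 − 1.960) = 78.2%.

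The gap between 60 and 63 is a separate matter and does not bear on this point. The 60 per group is used below only as a base.

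**3. Bias if only controls are excluded**

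Let q be the share of controls excluded, and D the difference in mean CAT change between excluded and retained controls. If r is the retained mean, the full control mean is (1 − q)r + q(r + D) = r + qD. Exclusion therefore shifts the control mean, and hence the treatment difference, by q × D in size. The documents give neither q nor D, so both are assumed.

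The standard error is 5 × √(1/[60(1 − q)] + 1/60). The last column is the chance of a two-sided significant result when there is no true difference in the full randomised population.

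| q | D (points) | Bias (points) | Share of 2.5 | Type I error |
|---|---|---|---|---|
| 0% | any | 0 | 0% | 5.0% |
| 5% | 1 | 0.05 | 2% | 5.0% |
| 10% | 3 | 0.3 | 12% | 6.2% |
| 20% | 3 | 0.6 | 24% | 9.5% |
| 20% | 5 | 1.0 | 40% | 17.8% |

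Example for the third row: SE = 5 × √(1/54 + 1/60) = 0.938 and 0.3/0.938 = 0.32. The error is then [1 − Φ(1.960 − 0.32)] + Φ(−1.960 − 0.32) = 6.2%.

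**4. Direction**

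A higher CAT score is worse. If excluded controls did worse than the rest, because they were sicker at referral, removing them flatters the control arm and hides benefit. If they did better, because rehabilitation helped, removing them exaggerates benefit. The sign cannot be predicted.

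**5. If both arms are excluded**

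The shift becomes q_C·D_C − q_I·D_I, with C for control and I for intervention. It vanishes only if the two products are equal, which randomisation does not guarantee because referral comes afterwards.

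**6. Power**

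From 60 per arm, excluding 5%, 10%, 20% or 30% of controls takes power from 78.2% to 77.1%, 76.0%, 73.3% or 70.0%. For 10%: Φ(2.5/0.938 − 1.960) = 76.0%.

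**The case against.** The strongest reply is that the usual-care sentence is a drafting slip. With the word not removed, it becomes a correct statement of ITT. The analysis section is the natural place to look for the analysis population, and it already protects the primary result. On that reading nobody is wrongly dropped. This is plausible, and it makes the harm conditional on the usual-care text being followed. It does not remove the fault: the document does not say which section governs, and a slip that defines who enters the primary analysis needs correcting.

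Second, the sentence says patients, not controls. The control-only reading comes from its heading and the sentences around it. It is the natural reading but not an explicit one. Excluding both arms would still be a post-randomisation selection and would still contradict the analysis section.

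Third, the protocol expects participants not to need rehabilitation, so q may be close to zero and the bias negligible. That stands, and the illustrative range therefore starts at zero. The expectation comes without a rate, however, and the protocol still considered the case likely enough to write a rule for it.

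Fourth, the loss of power is small: about two percentage points at 10% exclusion. That also stands, and the point does not rest on it.

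**Conclusion.** The concern holds. The usual-care section states an exclusion that ITT forbids, gives ITT as its reason, and conflicts with the analysis section on analysis, arm and trigger. That contradiction is established from the text alone and leaves the population for the primary outcome undetermined. It should be resolved before outcome data are seen, since otherwise the population could be chosen with the results in view.

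The numerical consequence is conditional. It arises only if the usual-care text is followed, and its size depends on assumed values of q and D. Over the values tabulated, the bias runs from nil to 1.0 CAT point against a target of 2.5, with unknown sign. The arithmetic shows that the error can matter, not that it will.

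**What to change.** In the usual-care section, replace the exclusion with a statement that participants in either arm who are referred to or receive pulmonary rehabilitation remain in the primary ITT analysis in their randomised arm.

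In the Quantitative analysis section, keep the exclusion only as a pre-specified sensitivity analysis. Use one trigger, identical in both arms; receipt is already the wording there. State that the resulting comparison is not protected by randomisation, and drop the post hoc label, since the analysis is planned. Report rehabilitation uptake by arm so that readers can judge how far it affects the contrast.

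The cost is a few sentences, with no additional patients and no change to access to rehabilitation. The schedule in Table 3 makes no exception for referred patients, but the article does not say outright that they continue to attend. One clause should confirm that their 6- and 9-month assessments are still collected.
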